## Abstract

**Background:**

Hemorrhoidectomy is associated with intense postoperative pain that requires multimodal analgesia. It includes nonsteroidal anti-inflammatory drugs (NSAIDs), acetaminophen, and local anesthetics to reach adequate pain control. There are data in literature preemptive analgesia could decrease postoperative pain after hemorrhoidectomy. The aim of this study is to assess the efficacy of preemptive analgesia with ketoprofen 100 mg 2 h before procedure per os with spinal anesthesia to decrease postoperative pain according to visual analog scale and to reduce the opioids and other analgesics consumption.

**Methods:**

Patients of our clinic who meet the following inclusion criteria are included: hemorrhoids grade III–IV and the planned Milligan-Morgan hemorrhoidectomy. After signing the consent all participants are randomly divided into 2 groups: the first one gets a tablet with 100 mg ketoprofen, the second one gets a tablet containing starch per os 2 h before surgery (72 participants per arm). Patients of both arms receive spinal anesthesia and undergo open hemorrhoidectomy. Following the procedure the primary and secondary outcomes are evaluated: opioid administration intake, the pain at rest and during defecation, duration, and frequency of other analgesics intake, readmission rate, overall quality of life, time from the procedure to returning to work, and the complications rate.

**Discussion:**

Multimodality pain management has been shown to improve pain control and decrease opioid intake in patients after hemorrhoidectomy in several studies. Gabapentin can be considered as an alternative approach to pain control as NSAIDs have limitative adverse effects. Systemic admission of ketorolac with local anesthetics also showed significant efficacy in patients undergoing anorectal surgery. We hope to prove the efficacy of multimodal analgesia including preemptive one for patients undergoing excisional hemorrhoidectomy that will help to hold postoperative pain levels no more than 3–4 points on VAS with minimal consumption of opioid analgesics.

**Trial registration:**

ClinicalTrial.govNCT04361695. Registered on April 24, 2020, version 1.0.

**Supplementary Information:**

The online version contains supplementary material available at 10.1186/s13063-022-06107-0.

## Background

Anorectal diseases are mostly benign and do not affect life expectancy, so currently both patients and clinicians are extremely interested in performing day care surgery. Anorectal surgery itself causes certain discomfort, especially pain, long recovery period, and a decreasing quality of life for several months.

The pain appears as a result of endogenous and exogenous factors affecting on the peripheral nerves endings, and also the pathological central nervous system excitation. Any surgical intervention activates nociceptors with various stimuli including mechanical factors as a result of a prick or cut of the tissue, chemical factors as a result of exposure to inflammatory mediators, and thermal factors as a result of heating or cooling the tissue [1]. Thus, any surgery is always accompanied by a pain syndrome with various pain severities.

In anorectal surgery, almost every patient experiences moderate/severe pain in the postoperative period, 12% of patients have severe pain throughout the recovery period, and control of postoperative pain is still problematic in 5% of cases when a severe pain syndrome continues despite standard pain management. It leads to long hospital admission and to an opioid intake increase [2]. The problem of analgesia is still relevant for patients after anorectal surgery, because the diseases affect more than 50% of the population over 50 years [3]. Excisional hemorrhoidectomy is the most effective method of stage III–IV hemorrhoidal disease treatment. However it is associated with intense postoperative pain which decreases significantly the quality of life in the postoperative period and overall patients’ satisfaction with treatment, increases time spent in hospital, and opioid analgesics consumption [2, 4]. The pain after hemorrhoidectomy (HE) and other anorectal surgery depends on anal sphincter and puborectal muscles spasm, the type of intra- and postoperative anesthesia, wound healing, surgical technique, stool type, and patient’s subjective perception [5, 6]. According to pain management international guidelines, the target level of postoperative pain should be 3–4 or less visual analog score (VAS) points [7].

Preemptive analgesia is aimed to prevent pain after surgery and affects several points of the “pain” cascade [2]. The most common non-narcotic analgesics that block peripheral pain perception include NSAIDs, corticosteroids, and acetylsalicylic acid. Non-narcotic drugs that inhibit central sensitization include ketamine, acetaminophen, and some anticonvulsants (in particular, gabapentin). So multimodal analgesia could theoretically reduce pain to a minimum due to blocking all kinds of pain receptors. However, the preoperative use of even one type of analgesic contributes to pain relief and to the opioid consumption decrease after the intervention [8–11].

One of the most commonly prescribed painkillers is non-steroidal anti-inflammatory drugs (NSAIDs), which have an adequate analgesic effect and even in acute pain can reduce the opioid dose by 18.3% [12]. Regarding ketoprofen as an analgesic drug, none of the published studies describes anorectal surgery. However, ketoprofen is widely used in spinal, orthopedic, general, dental, and children surgery with successful outcomes [13–16]. It also showed significant efficacy as preemptive analgesia compared to the other drugs [17]. Ketoprofen is approved for use as an analgesic for the treatment of mild to severe pain in the postoperative period in total daily doses up to 300 mg; the recommended initial dose is 25 to 100 mg (the dosages are intended for people without acute or decompensated concomitant diseases or non-pregnant women) [18]. Comparing ketoprofen to acetaminophen, the first one showed a significantly better anti-inflammatory effect on the 3rd and 6th day after surgery and lower pain intensity [19].

Therefore adequate postoperative analgesia requires the multimodal approach including opioid analgesics, nonsteroidal anti-inflammatory drugs (NSAIDs), acetaminophen, and local anesthetics. But there is no current standard on preemptive analgesia for adult patients with symptomatic hemorrhoids grade III–IV undergoing Milligan-Morgan hemorrhoidectomy without previous history of anorectal interventions and decompensated somatic diseases, although several studies report some regimens that seem to be effective.

## Methods

### Objective

The aim is to assess the efficacy of preemptive analgesia with Ketoprofen 100 mg 2 h before procedure per os with spinal anesthesia to decrease postoperative pain according to visual analog scale and to reduce the opioids and other analgesics consumption.

### Study design and setting

This is a prospective, randomized, double-blind, unicenter, superiority, parallel-group 2-arm study with 1:1 allocation ratio conducted in the surgical department of Moscow Research Educational Center of the Lomonosov Moscow State University. It is in the recruitment stage. We are anticipating 144 patients of all genders from 18 to 75 years old in total who come to the clinic. Thus, in this case, a uni-center design can assure sufficient patient recruitment.

### Eligibility criteria

Every patient included in the study must meet the following criteria:
Symptomatic hemorrhoids grade III–IVPlanned surgery: Milligan-Morgan hemorrhoidectomy

Patients who had contraindication or technical inability to perform subarachnoid anesthesia or other somatic diseases (history of peptic ulcer diseases and gastrointestinal bleeding and other acute or decompensated organ pathology) or refused to participate and pregnant women are not included. The written voluntary informed consent to participate (Additional file 3) is obtained from all eligible patients before randomization.

### Interventions

#### Preoperative preparation

Two hours before the procedure, every patient receives a medication. The research group receives ketoprofen 100 mg per os; the control group receives a placebo.

#### Surgical technique

Under spinal anesthesia, the patient is placed in a modified lithotomy position on the back, with legs spread apart on supports. During anesthesia, the patient is sitting. The needle is inserted between L3 and L4 space or L4 and L5 space. We usually use a bupivacaine solution 5 mg/ml for spinal anesthesia. No adjuvant medicaments are used. The operative field is treated with an antiseptic solution twice and draped. A complex of external and internal hemorrhoids or internal hemorrhoids only is excised with monopolar electrocautery or bipolar electrosurgery device. Hemorrhoid pedicle is tied with an absorbable polyfilament suture, and then the pedicle is crossed by monopolar or bipolar electrocautery. The wound is not sutured. One, two, or three nodes can be removed per procedure depending on the number of the enlarged hemorrhoidal nodes.

#### Postoperative period

After the procedure, all patients receive the standard analgesics scheme. It includes ketoprofen (the average dose, 100 mg per day; the maximum dose, 200 mg per day), paracetamol (at the maximum dose of 1000 mg per day), and local anesthetics with lidocaine before defecation. Patients are usually discharged on the 4–5th day after surgery when their pain level is below 5 points according to VAS. After discharge, a standard analgesics scheme mentioned above is recommended to all patients. If the pain level reaches 5–6 points according to VAS on the 5th day after the procedure, patients continue inpatient treatment and may receive an opioid analgesic.

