### Sample size

Considering that this is a superiority study, the sample size was calculated using a 1-sided Blackwelder test. According to published data, the incidence of opioid intake after hemorrhoidectomy varies from 20 to 30% [7]. The expected incidence of opioid intake after hemorrhoidectomy with preemptive analgesia is not more than 10%. The purpose of this study is to show that the opioids intake in patients with preemptive analgesia is lower than without it. Considering that *a* = 0.05. the statistical power of the study is 80%, the patients are randomized into 2 groups with 1:1 allocation ratio, the noninferiority margin *D* = 5%, and the required sample size is 144 patients (72 patients in each of the 2 groups).

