## Discussion

Multimodality pain management for anorectal surgery has been shown to improve pain control and decrease opioid requirements in several studies. Preoperative oral acetaminophen and gabapentin admission followed by intravenous ketamine in the early postoperative period resulted to significantly less pain level postoperatively and decreased narcotics intake [2]. Place RJ [20] showed a significant decrease of postoperative analgesics requirement in addition to reducing voiding problems by systemic admission of ketorolac with local anesthetics in patients undergoing anorectal surgery.

Several studies showed that ketoprofen significantly reduced opioid consumption (by 33%) and improved postoperative analgesia after spinal and abdominal surgery [13–16]. Patients with acute pain who have undergone dental surgery get a meaningful pain relief, a faster onset of effect, the highest peak effect, and the longest duration of action using ketoprofen than other NSAIDs and analgesics [18, 21]. In all mentioned above studies, adverse effects related to ketoprofen were minor and infrequent.

We hope to prove the efficacy of multimodal analgesia including preemptive one for patients undergoing excisional hemorrhoidectomy that will help to hold postoperative pain levels no more than 3-4 points on VAS with minimal consumption of opioid analgesics.

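### The randomised contrast is one preoperative ketoprofen tablet on a scheme that already contains ketoprofen; the stated 80% power is not met over the lower part of the assumed range, and the hoped-for conclusion about multimodal analgesia is not what is tested

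*Protocol article*

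**What the plan says.** **Treatment.** The protocol article, under Preoperative preparation, defines the randomised difference: "The research group receives ketoprofen 100 mg per os; the control group receives a placebo". Under Postoperative period, "all patients receive the standard analgesics scheme. It includes ketoprofen (the average dose, 100 mg per day; the maximum dose, 200 mg per day"), together with paracetamol and lidocaine before defecation. This continues at home: "After discharge, a standard analgesics scheme mentioned above is recommended to all patients".

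**Sizing.** Sample size cites published data for the control rate: "the incidence of opioid intake after hemorrhoidectomy varies from 20 to 30" per cent. For the other arm it says, without a reference, "The expected incidence of opioid intake after hemorrhoidectomy with preemptive analgesia is not more than 10" per cent. It names a one-sided Blackwelder test, alpha 0.05, 80% power and a margin D of 5%, and arrives at 72 per arm.

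**Effects cited elsewhere.** Background says of NSAIDs in general that they "even in acute pain can reduce the opioid dose by 18.3" per cent. The Discussion adds, for spinal and abdominal surgery: "Several studies showed that ketoprofen significantly reduced opioid consumption (by 33" per cent).

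**Conclusion sought.** The Objective is narrow: preemptive ketoprofen 100 mg two hours before the procedure. The Discussion closes more broadly, and the Abstract says the same: "We hope to prove the efficacy of multimodal analgesia including preemptive one for patients undergoing excisional hemorrhoidectomy".

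**The concern.** Two statements in the article do not fit the comparison that is randomised.

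The first is the sizing. The control arm is not free of ketoprofen, so the effect to be detected is what one preoperative tablet adds to a scheme that already contains the drug. Sample size does not say whether the cited 20–30% was observed under such a scheme. Nor does it say why one added dose should bring the rate to 10% or below. A single figure of 80% power is attached to a range of control rates over which power varies widely.

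The second is the conclusion. Every patient receives the multimodal scheme, so no randomised comparison bears on whether that scheme works.

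At stake is how the result will be read. If the true control rate is near 20%, a real halving of opioid use would be missed about half the time, while readers would believe the chance was one in five. A positive result would be reported as support for more than was tested.

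**Working it through.** **Inputs.** From Sample size: control rate 20–30%, treated rate at most 10% (taken as exactly 10%), one-sided alpha 0.05, power 80%, D = 5%, 72 per arm. From the Discussion: 33% less opioid consumption. The 25% is the midpoint of the stated range.

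**Assumed relative cut.** 1 − 10/20 = 50%; 1 − 10/30 = 67%. These are minima, since the plan says not more than 10%.

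**Reproducing 72 per arm.** The Blackwelder form is n = V(z₀.₉₅ + z₀.₈₀)² / (p_c − p_t + D)², with (1.645 + 0.842)² ≈ 6.18.
- 20% vs 10%, D added to the difference as a true non-inferiority margin, pooled variance V = 2 × 0.15 × 0.85 = 0.255: 0.255 × 6.18 / 0.15² = 70.1, so 71 per arm. With unpooled V = 0.16 + 0.09 = 0.25 it is 69.
- D as a superiority margin (subtracted): 619 per arm at 20% vs 10%, and 83 at 30% vs 10%.
- 30% vs 10%, two-sided, continuity-corrected, no margin: exactly 72, but this ignores both the stated one-sided test and D.

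So the stated design comes close to 72 only if the trial is sized to show that ketoprofen is not worse by more than 5 points. On that reading, power at 20% vs 10% is 81%. The article describes a superiority study that aims to show lower opioid intake. How D is used is a separate matter; here the question is what 72 per arm gives for superiority.

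**Superiority power at 72 per arm.** Power = Φ{[ (p_c − p_t)√n − z√(2p̄(1 − p̄)) ] / √(p_c(1 − p_c) + p_t(1 − p_t))}, with p̄ the mean of the two rates and z = 1.645 (one-sided) or 1.960 (two-sided).

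Example, 20% vs 10%, one-sided: (0.10 × 8.485 − 1.645 × 0.505) / 0.500 = 0.036, and Φ(0.036) = 0.51.

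| Control rate | Treated rate | One-sided 5% | Two-sided 5% |
|---|---|---|---|
| 20% | 10% | 51% | 39% |
| 25% | 10% | 77% | 66% |
| 30% | 10% | 92% | 86% |

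The same formula gives 81% one-sided at a control rate of 26%, so 80% is reached only from about 26% upwards.

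**Sensitivity case.** Suppose the 33% cut in consumption carried over unchanged to incidence, so that p_t = 0.67 × p_c:

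| Control rate | Treated rate | One-sided 5% | Two-sided 5% |
|---|---|---|---|
| 20% | 13.4% | 28% | 18% |
| 25% | 16.75% | 33% | 23% |
| 30% | 20.1% | 39% | 28% |

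**Conclusion against contrast.** The Objective names the preoperative tablet. Preoperative preparation randomises that tablet and nothing else. Postoperative period gives the multimodal scheme to everyone. The closing sentence of the Discussion, and the matching one in the Abstract, go beyond all three.

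**The case against.** The best defence is that an add-on, placebo-controlled design on common background care is legitimate and that the Objective already names the narrow question. Both are true. The background treatment is not at fault, and the multimodal wording is an expressed hope, not a stated hypothesis. It does appear twice, however, and as the closing message each time, so it is worth correcting.

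A second defence is that the 33% and 18.3% are reductions in opioid amount, in other settings, whereas the sizing uses the proportion of patients taking any opioid. This also stands. A cut in mean amount does not fix the cut in incidence, which is why the 33% appears above only as a sensitivity case. The main result does not use it.

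A reader might go further in three ways that the documents do not support.
- *That a null result is likely.* This needs the cited reductions to apply to incidence after hemorrhoidectomy, which nothing in the article shows.
- *That the 10% was taken from a larger contrast, such as ketoprofen against none.* The figure has no source, so its origin cannot be known. The article attaches it to preemptive analgesia.
- *That the trial claims to separate preoperative timing from total dose and cannot.* No section makes that claim. The extra total exposure is not established either: the postoperative doses are an average and a maximum, and other analgesic intake is itself a secondary outcome that may differ by arm.

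Finally, two-sided figures should not lead, because Sample size declares a one-sided test. The shortfall remains on the one-sided figures.

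**Conclusion.** The point holds in this form. The randomised contrast is one preoperative ketoprofen tablet or placebo, added to a scheme that already contains ketoprofen in both arms. Against the unsourced 10%, 72 per arm gives one-sided superiority power from about 51% to 92% across the plan's own control rates, and falls short of 80% below about 26%. The sensitivity case at a 33% relative cut gives 28–39% one-sided, conditional on the carry-over assumption. The hoped-for conclusion about multimodal analgesia exceeds both the Objective and the comparison.

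The main power figures assume a plain test of two proportions by normal approximation, all 72 per arm analysed, and a treated rate of exactly 10%; a lower treated rate would raise power. They concern incidence of opioid use, the quantity used for sizing, and do not give the power of an analysis of opioid amount per day.

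**What to change.** **Sample size.** State that the contrast is one preoperative ketoprofen 100 mg tablet against placebo, added to a standard postoperative scheme that includes ketoprofen in both arms. State the control rate assumed under that scheme and the basis for the 10%. Replace the single 80% with power at 72 per arm over the stated range on the declared test (about 51%, 77% and 92% one-sided at 20%, 25% and 30% vs 10%). Add the smaller effect as a labelled sensitivity case (about 28–39% one-sided).

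**Abstract and Discussion.** Replace the hope of proving multimodal analgesia with the efficacy of adding a preoperative ketoprofen 100 mg tablet to the standard postoperative scheme, in line with the Objective.

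**Cost.** Wording in three places, with no change to treatment, patients or data. The stated power becomes less favourable and the claim narrower.

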### The main outcome measures

The trial is conducted to evaluate the primary outcome: the quantity of the opioid administration intake per day during the first week postoperatively that is necessary to hold pain level no more than 3–4 VAS points in every patient. We use tramadol as an opioid analgesic in a single standard dose of 100 mg for patients with persistent severe pain syndrome in our clinic. The study also assesses the following secondary outcomes: (1) the pain severity before and after defecation according to VAS on the 6, 12, and 24 h after the procedure, then 2 times per day up to 7th postoperative day; (2) duration and (3) frequency of other analgesics intake (systemically and topically) during the first week postoperatively; (4) readmission rate and (5) overall quality of life on the 7th and 30th days; (6) time from the procedure to return to work; and (7) the complications rate (i.e. bleeding, retention of urine, infectious complications) in the early postoperative period (30 days after procedure). The pain severity, duration and frequency of other analgesics intake during the first week postoperatively will be assessed using “Postoperative protocol for pain management” (Additional file 2). The overall quality of life will be assessed with a patient-reported questionnaire Short Form 36 (SF-36). A total score in each of the 8 sections will be calculated and transformed into a 0–100 scale with a score of zero equivalents to maximum disability and a score of 100 equivalents to no disability. Other secondary outcomes will be updated during visits or by phone on the 7 and 30 days after the surgery.

All patients are scheduled to return to the ambulatory clinic on the 7 and 30 days after the surgery. During these visits, postoperative data is collected and digital rectal examination is performed. If a patient fails to follow up, the researcher may contact the patient by all means available (phone, email, or mail) to ascertain whether the patient has had any complications and/or adverse events that were treated at another hospital. If the researcher is unsuccessful in contacting the patient, the patient will be considered as lost to follow-up.

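### The opioid rule under Postoperative period does not match the primary outcome it is meant to generate, and the 20–30% planning rate is not tied to either

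*Protocol article*

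**What the plan says.** All references are to the Protocol article.

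- **The main outcome measures** defines the primary outcome as "the quantity of the opioid administration intake per day during the first week postoperatively that is necessary to hold pain level no more than" a set ceiling, which is VAS 3–4 and applies to each patient. It adds: "We use tramadol as an opioid analgesic in a single standard dose of 100 mg for patients with persistent severe pain syndrome". That sentence gives neither a day nor a VAS value.
- **Postoperative period** begins "After the procedure, all patients receive the standard analgesics scheme" and lists ketoprofen, paracetamol and lidocaine. Discharge is usually on day 4–5, once VAS is below 5. For the time at home: "After discharge, a standard analgesics scheme mentioned above is recommended to all patients". The section's one reference to an opioid concerns patients with a VAS score of 5–6: "on the 5th day after the procedure, patients continue inpatient treatment and may receive an opioid analgesic".
- **Sample size** plans on an incidence of opioid use, not a daily quantity: "the incidence of opioid intake after hemorrhoidectomy varies from 20 to 30"%, attributed to published data, against at most 10% with preemptive ketoprofen, giving 72 per arm.
- **Preoperative preparation** gives the study drug as one dose 2 h before surgery.

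**The concern.** Opioid intake is an outcome created by a treatment decision. It measures pain only as well as the rule that triggers the drug, and that rule must be the same for everyone. Here the section that defines the outcome and the section that describes care give different triggers. Three things are at stake:

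- what the primary outcome means;
- whether two patients with the same pain receive the same value;
- whether the planning rate, taken from published data, describes patients treated under this trial's rule.

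**Working it through.** **Step 1. The two sections side by side.**

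| Feature | The main outcome measures | Postoperative period |
|---|---|---|
| Day | each day of week 1; tramadol sentence has no day limit | day 5 |
| Pain level | hold VAS at no more than 3–4; separately, an undefined persistent severe pain | VAS 5–6 |
| Who | every patient | patients kept in hospital |
| Obligation | the quantity necessary to reach the target | may receive |

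**Step 2. A patient who falls between them.** Take VAS 4.5 on day 4. This is above the outcome's target of 3–4. It is below 5, so discharge is allowed, on a scheme that lists no opioid. It is also below the 5–6 at which an opioid is mentioned, and is not obviously persistent severe pain. The patient contributes zero opioid although the target was missed. For such patients the recorded quantity is not the quantity needed to hold VAS at 3–4.

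**Step 3. The window on a literal reading.** If staff follow Postoperative period alone, opioid use can arise only from day 5 and only in patients still in hospital. Days 1–4 and all discharged patients then count as zero, although the study drug is a single preoperative dose. The section does not forbid earlier use, so this is one possible reading.

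**Step 4. The plan's own sample size.** Blackwelder formula, one-sided α = 0.05, power 80%, control 20%, treated 10%, D = 5% used as a non-inferiority margin, pooled variance with mean rate 0.15:

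n = 2 × 0.15 × 0.85 × (1.645 + 0.842)² / (0.10 + 0.05)² = 0.255 × 6.183 / 0.0225 = 70.1, rounded up to 71 per arm (142 in total), close to the stated 72 and 144.

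The unpooled variance gives 69. A two-sided, continuity-corrected calculation at 30% vs 10% gives exactly 72, but uses neither the stated one-sided test nor the margin. Tested for plain superiority without a margin (one-sided 5%, normal approximation), 72 per arm has power 51%, 77% and 92% at control rates of 20%, 25% and 30% against 10%. The plan is therefore sensitive to the control rate even within its own range. (The use of a non-inferiority margin in a superiority trial is a separate matter.)

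**Step 5. Sensitivity to a lower control rate.** The document gives no opioid rate under its own rule. As anchors only, Background reports that 12% of anorectal surgery patients have severe pain throughout recovery, and that "control of postoperative pain is still problematic in 5% of cases when a severe pain syndrome continues despite standard pain management". The treated rates below are assumed to be half the control rate in the last two rows. Power is by exact enumeration of two binomials, 72 per arm, counting rejections that favour ketoprofen.

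| Control vs treated | Expected control events | Two-sided Pearson | Two-sided Fisher | One-sided Pearson |
|---|---|---|---|---|
| 20% vs 10% (plan, lower end) | 72 × 0.20 = 14.4 | 39% | 32% | 53% |
| 12% vs 6% (assumed) | 72 × 0.12 = 8.6 | 24% | 16% | 36% |
| 5% vs 2.5% (assumed) | 72 × 0.05 = 3.6 | 11% | 3% | 22% |

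Both one- and two-sided results are shown because Sample size uses a one-sided test and Statistics names only a 5% level.

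**The case against.** The sections can be read together: the tramadol sentence as the general rule, with no day limit, and the day-5 sentence as what happens when a patient is not fit for discharge. The day-5 sentence does not say an opioid is given only then. Background also lists opioids within multimodal analgesia. This stands, and it rules out a stronger reading that a reader might infer: that the outcome is close to zero by design and cannot register early opioid use. The documents do not establish that.

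Nor do they support calling the 20–30% rate baseless. It has a citation; what is missing is a statement that it applies under this trial's opioid rule. The 5% and 12% are weak proxies: they count severe pain after anorectal surgery in general, not opioid use after hemorrhoidectomy, and a VAS 5–6 trigger might capture more patients. The treated limit of 10% is an upper bound, so a control rate below 10% would not by itself contradict it. The trial is single-centre, so the risk is inconsistency between staff, or over time, within one department.

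The objection does not remove the conflict. Even the combined reading leaves persistent severe pain undefined, and neither trigger corresponds to a target of 3–4.

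**Conclusion.** The contradiction stands and needs no outside figure: day, threshold, setting and obligation differ between the section that defines the primary outcome and the section that describes the care generating it. This is more than condensed detail, because both sections state a rule and the rules disagree. Followed as written, the plan does not measure the outcome it names.

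The effect on power is not established. The control rate under the trial's rule cannot be computed from the document, and the 24% and 11% figures rest on assumed rates. They show only that, if the true rate is well below 20–30%, power with 72 per arm would be far under the planned 80%. The case for correction rests on the definition of the primary outcome, not on a demonstrated loss of power.

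**What to change.** 1. Reconcile Postoperative period and The main outcome measures into one statement of when, in whom and until which day an opioid can be given, applied identically in both arms. The clinical team decides the rule; none is proposed here.
2. Make the primary outcome definition and its time window agree with that statement. If the agreed rule confines opioid use to late in the week, say so openly, since the window would then lie further from the preoperative dose.
3. State whether the 20–30% incidence applies under the agreed rule. If it does not, restate the planning rate and the power.

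Reconciling the text costs an amendment and no extra study procedures. If the planning rate is then lowered, the sample size may have to be revisited. The Protocol article describes recruitment as running from April 2020 to an expected end in December 2021, so the amendment should also say from which date the agreed statement applies.
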